**5. RESEARCH METHODOLOGY**

**5.1 STUDY DESIGN AND METHODOLOGY**

Randomized Double Blind, Placebo Controlled Study

Study type: Interventional

This is a randomized, double-blind, placebo-controlled clinical trial. Recruitment of Parkinson disease patients with constipation will be done from the neurology clinic HUKM. Patients are considered eligible if they meet the Rome III criteria for functional constipation^33^ (2 or more criteria as listed in the box below in at least 25% occasion for the last 3 months) and will be provided written informed consent. Standard therapy for constipation is Syrup lactulose (osmotic agents) which promote intestinal motility and secretion. The recommended dose of lactulose for adults is 15 to 30 mL once or twice daily. The use of syrup lactulose is not forbidden and patient will be advised to take syrup lactulose as per needed. Fecal occult blood testing will be used to screen for colorectal malignancy in all eligible patients prior to intervention as positive test patients will not be included in the study. After written informed consent given, patients’ demographic data were collected.

|  | **6. HOSPITAL PROFILE/DEMOGRAPHIC**  **7. STUDY PERIOD**  June 2018 – June 2019  **8. SUBJECTS**  **8.1 TARGET POPULATION**  Patients with Parkinson disease attending the neurology outpatients clinic who fulfil inclusion and exclusion criteria  **9. SAMPLING**  **9.1 INCLUSION CRITERIA**   1. Idiopathic PD diagnosed using UK PD Society Brain Bank Criteria 2. Diagnosis of constipation according to Rome III Functional Constipation Criteria 3. Written informed consent   **ROME III Diagnostic Criteria : Functional Constipation**   \| Functional Constipation \| \| --- \| \| Must include 2 or more of the following:  Straining *  Lumpy or hard stools*  Sensation of incomplete evacuation*  Sensation of anorectal obstruction/blockage*  Manual manoeuvres to facilitate defecation(digital evacuation, support of pelvic floor)*  <3 defecation per week*  ***≥25% of defecations**  Loose stool rarely present without use of laxatives  Insufficient criteria for IBS \|   Based on Longstreth GF et al.Gastroenterology 2006 ;130:1480-1491  **9.2 EXCLUSION CRITERIA**   1. Secondary Parkinsonism 2. Previous history of small and large bowel disease 3. Previous extensive gastrointestinal tract surgery 4. Positive stool occult blood in the last 1 month 5. Use of probiotics or antibiotics in 2 weeks before baseline visit 6. Underlying Dementia 7. Hypothyroidism 8. Diagnosed with major depression and on antidepressant 9. Lactose intolerance   10. Type 1 and Type 2 DM  **10. DATA COLLECTION**  **10.1 METHOD OF DATA COLLECTION**  Patients with idiopathic PD attending the neurology outpatients’ clinic will be invited to participate in the study. All subjects will be screen for constipation by using Rome III Criteria – Constipation Module. Written informed consent will be obtained from all subjects after screening inclusion and exclusion criteria. Baseline demographic data will be recorded into a structured questionnaire.  Screening assessment :  1) Constipation screening using Rome III Criteria – Constipation Module  2) Fecal occult blood testing - negative test will be included in the study  The eligible subjects will be assess on the first visit as below :  1) Constipation symptoms by using Garrigues Constipation module (GQ)  2) Quality of life by using PDQ39 Questionnaire (self-administered malay version )  3) Parkinson Disease severity by using MDS-UPDRS  4)Non motor symptoms of PD by using NMS scale  (All the above questionnaires are validated)  Subsequently, subjects will be instructed to consume 4 red carmine capsule(food colourant) and once the stool turn red in colour, Gatrointestinal Transit Time(GTT) will be measured and recorded. Subjects will then receive a 3g sachet of either probiotics (containing multistrains of lactobacillus and Bifidobacterium 30 Colony Forming Unit) or placebo twice-daily for a duration of 8 weeks. Once consumption completed, subjects need to consume again another 4 red carmine capsule and GTT will be measured and recorded again. Final assessment will be done once subjects completed all the probiotics or placebo given(week 8) and subjects need to be assess again on constipation symptoms, non-motor symptoms, quality of life and disease severity same as done at baseline using the same questionnaire.  **10.2 STUDY PROTOCOL**  Randomization  All patients who fulfill inclusion and exclusion criteria will be stratified based on age, sex and background social economics. Patients who are enrolled will be randomized into two treatment groups which a probiotics group who will receive probiotics (containing multistrains of lactobacillus and Bifidobacterium 30 Colony Forming Unit) or placebo using blocks randomization method, in blocks of 4. Patients and investigator will remain blinded to the treatment protocol.  Following randomization, patients will receive their assigned treatment from the pharmacy department, Hospital Canselor Tuanku Muhriz, PPUKM  Treatment  Active treatment group will receive a 3 gram sachet of probiotics containing multistrains of lactobacillus and Bifidobacterium 30 Colony Forming Unit x 10^9^ to be taken twice daily for 8 weeks.  Composition of probiotics:   \| Lactobacillus acidophilus \| 107mg \| \| --- \| --- \| \| Lactobacillus casei \| 107mg \| \| Lactobacillus lactis \| 107mg \| \| Bifidobacterium bifidum \| 107mg \| \| Bifidobacterium infantis \| 107mg \| \| Bifidobacterium longum \| 107mg \|   Placebo group will receive a 3g sachet of substance (powder form) that has no therapeutic effect to be taken twice daily for 8 weeks.  All test products will be concealed in sealed envelopes, to ensure blindedness  **10.3 STUDY ASSESSMENT**  All patients will be assessed at baseline and week 8 for improvement in constipation symptoms using the Garrigues Constipation Questionnaire^35^, Quality of Life by using self- administered PDQ39 questionnaire (malay version)^36^, disease severity by using MDS-UPDRS and non-motor symptoms by using NMS scale . The Gastrointestinal transit time will be assessed at baseline and week 8 using red carmine capsule. Compliance to treatment, side effects and clinical assessments will be performed by a blinded assessor at baseline and week 8 for both groups.  **Gastrointestinal Transit Time Protocol**  Following randomization, subjects will be instructed to ingest 4 red carmine capsule after last bowel opening. Red carmine capsule is a food colorant and non-toxic to body which is used to measure GTT. The time of ingestion will be recorded. GTT is measured from the time of red carmine capsules consumption and first appearance of red colored stool. The duration from time of ingestion and appearance of red colored stool (Gastrointestinal transit time) will be recorded by patient at baseline, and week 8. The use of laxatives is not forbidden, but patients are required to use as per needed. GTT was measured during pre and end treatment in both groups.  **Constipation-Related Symptom Assessment**  Constipation related symptoms will be assessed using the Garrigues Constipation Questionnaire (GQ)^35^ which is a 21-item that was developed to define the presence of chronic constipation. Only 13 of the 21 items are related to bowel habits. The Rome 111 criteria were used to define constipation. The items are scored using two different four-point Likert scales. The first consisted of ‘never’, ‘sometimes’ (25% of the time) and ‘always’. The second consisted of ‘never’, ‘fewer than once a week’, ‘one or more times a week’ and ‘every day’. Total and cut off scores were not reported.  **Quality Of Life Assessment**  Baseline Quality of life patients will be assess using self-administered PDQ-39^36^ Questionnaire(Malay version) and end of intervention, subject will be assessed again using the same questionnaire. PDQ-39 questionnaire contains 39 items with each item was rated by the patients using one of five categories, from 0 (never) to 4 (always). PDQ-39 summary index (PDQSI) is calculated by dividing the sum of the total raw score by the maximum possible score (156 or 152 points, depending on the patient’s marriage status) and multiplying by 100. In this study, we will use PDQSI as a standardized index for representing PD patients’ life quality.  **Non Motor symptoms (NMS) assessment**  Severity of Non Motor symptoms of each individual will be assess using NMSS Questionnaire. Frequency and severity of each NMS are taken into account. Final total score of disability (0=no disability; 360=maximal disability).  **DDisease severity assessment**  Parkinson Disease severity assessment will be assess using MDS-UPDRS questionnaire. MDS UPDRS has four parts which include nonmotor experiences of daily living (13 items), motor experiences of daily living (13 items), motor examination (18 items), and motor complications (six items). Each subscale now has 0-4 ratings, where 0 = normal, 1 = slight, 2 = mild, 3 = moderate, and 4 = severe.  10.4 **VALIDITY OF TOOLS**  NMS and MDS-UPDRS are public domain questionnaire  Validated score : PDQ 39 (malay version)- permission obtained from author  Garrigues Constipation Questionnaire- awaiting permission from author  **11. STASTICAL ANALYSIS**  Statistical Package for the Social Sciences (SPSS) Software version 2 will be used for statistical analysis. Age, height, weight, body mass index (BMI) and gender were compared between the groups by Student’s t-test and the chi-squared test. General Linear Model will be used to compare intestinal transit time in probiotics and placebo groups before and after 8 weeks of intervention. Pre- and post-probiotics consumption data on clinical evaluation of constipation that will be obtained from all the questionnaires namely Rome III criteria, PDQ-39 Questionnaire and Garrigues Constipation Questionnaire will be analysed using Mc Nemar Test. Independent t-test will be used to compare the differences of intestinal transit time in both groups. Pearson correlation and Simple linear regression analysis will be utilized to explore the relationship and effect between two numerical variables. A p-value <0.05 will be considered as statistically significant.  **11.1 SAMPLE SIZE CALCULATION**  The sample size is being calculated based formula comparing between two proportions. Sample size calculation was performed according to a study by Sakai et al^32^ based on value reported on changes in percentage of bowel movements and complete bowel movements after 3 weeks of probiotics treatment where there was a significant decreased from 73.7% to 36.8%,  Formula for sample size comparing two proportions:  [figure not shown]  Sample size was estimated as follows :  p1 = 0.737  p2 = 0.368  zα = 1.96  zβ = 0.84  n = 0.737 (1 – 0.737) + 0.368 (1 – 0.368 ) X (1.96 + 0.84) ^2^  (0.737 – 0.368) ^2^  n = 0.193831 + 0.232576 X 7.84  0.136161  n = 25 per group  The number of samples per group is further added 20% to compensate for non-response and lost to follow up. The final samples required for each group is 30 patients. |
| --- | --- | --- | --- | --- | --- | --- | --- | --- | --- | --- | --- | --- | --- | --- | --- |
|  | **12. Study Flow Chart**  **1^ST^ VISIT- WEEK 0**  Patients (n= 60)  Constipation assessment with GQ  Quality of life assessment with PDQ39  Disease severity assessment with MD S- UPDRS  Non motor symptoms assessment with NMS  Probiotics (n=30)  Placebo (n=30)  RE-ASSESSMENT POST INTERVENTION |

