**4. OBJECTIVE**

**4.1 PRIMARY OBJECTIVE**

- To determine the effects of probiotics (multistrains of Lactobacillus and Bifidobacterium ) on constipation among Parkinson disease patients compared to placebo
- To determine the effects of probiotics on Gastrointestinal Transit Time (GTT) compared to placebo

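### Section 11 names no between-arm test for constipation symptoms, so the first primary objective, a comparison with placebo, has no analysis that answers it

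*Combined protocol and SAP*

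**What the plan says.** Section 4.1 sets two primary objectives. The first is the effect of probiotics "on constipation among Parkinson disease patients compared to placebo"; the second is transit time, also against placebo.

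Section 5.1 sets the clinical background. On entry, "Patients are considered eligible if they meet the Rome III criteria for functional constipation". On laxatives, "Standard therapy for constipation is Syrup lactulose (osmotic agents) which promote intestinal motility and secretion", and "The use of syrup lactulose is not forbidden and patient will be advised to take syrup lactulose as per needed". The permission is the same for both arms.

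Section 10.3 gives the Garrigues questionnaire at baseline and week 8. It has four-point items, and "Total and cut off scores were not reported".

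Section 11 assigns the tests:
- Transit time: a General Linear Model on the two groups before and after treatment, and "Independent t-test will be used to compare the differences of intestinal transit time in both groups".
- Constipation: "Pre- and post-probiotics consumption data on clinical evaluation of constipation", drawn from Rome III, PDQ-39 and Garrigues. The sentence ends "Garrigues Constipation Questionnaire will be analysed using Mc Nemar Test".
- Age, height, weight, BMI and gender: t-test and chi-squared test between groups.
- Pearson correlation and simple linear regression for pairs of numerical variables.

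Section 11.1 sizes the trial with a formula for two independent proportions, 73.7% and 36.8%, giving 25 per group and 30 after a 20% addition.

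**The concern.** McNemar is a paired test. It asks whether more patients in one set changed from constipated to not constipated than the reverse. Placebo patients do not enter it as a comparator. Improvement from placebo response, from regression to the mean in patients selected for being constipated, or from lactulose taken during the 8 weeks counts in the same way as improvement from the probiotic.

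Randomisation and blinding deal with all of these, but only if the arms are compared. Followed as written, the plan could report a significant improvement in constipation that owes nothing to the product, while giving no symptom result against placebo.

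**Working it through.** **1. The plan's own sample size.** Inputs from section 11.1: p1 = 0.737, p2 = 0.368, z values 1.96 and 0.84.

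n = [0.737 × 0.263 + 0.368 × 0.632] × (1.96 + 0.84)² / (0.737 − 0.368)² = (0.193831 + 0.232576) × 7.84 / 0.136161 = 24.55, so 25; and 25 × 1.2 = 30.

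The figure reproduces. The formula belongs to a comparison of two independent groups, which section 11 does not name for any symptom outcome.

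**2. McNemar in the probiotic arm when the probiotic does nothing.** Let b patients improve and c worsen. The exact two-sided p-value is 2 × P(Binomial(b + c, 0.5) ≤ min(b, c)). If nobody worsens, significance needs b ≥ 6, since 2 × 0.5⁵ = 0.0625 and 2 × 0.5⁶ = 0.031. For example, P(Binomial(25, 0.20) ≥ 6) = 38%. With worsening, sum the multinomial probabilities of all (b, c) that are significant with b > c. The rates are assumptions, as shares of the whole arm:

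| Improve / worsen | n = 25 | n = 30 |
|---|---|---|
| 10% / 10% | 0.4% | 0.6% |
| 10% / 0% | 3% | 7% |
| 20% / 10% | 7% | 9% |
| 20% / 5% | 17% | 24% |
| 30% / 5% | 46% | 57% |
| 20% / 0% | 38% | 57% |
| 30% / 0% | 81% | 92% |

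The reference value for a valid 5% two-sided test, counting only results that favour the probiotic, is 2.5%. Worsening needs patients who were not constipated at baseline on the chosen definition. Rome III entry makes them a minority, but Garrigues status may not agree exactly with Rome III.

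**3. Running McNemar in each arm and comparing the verdicts.** If each arm is significant with probability s, the chance that the probiotic arm is significant and the placebo arm is not is s(1 − s). With 25 per arm this is 0.165 × 0.835 = 14% (20%/5%), 0.457 × 0.543 = 25% (30%/5%), 0.383 × 0.617 = 24% (20%/0%) and 0.807 × 0.193 = 16% (30%/0%), all with no probiotic effect.

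**4. A between-arm test on the same null.** With 25 per arm and 80% or 70% still constipated in both arms, full enumeration of the uncorrected chi-squared test gives 5.5% or 5.4% in either direction, about half of it favouring the probiotic. Simulation over other equal rates gave about 5 to 6%.

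**5. Power of that test at the plan's effect.** At 73.7% versus 36.8%, enumeration gives 80% with 25 per arm and 84% with 30. Fisher's exact test gives 71% and 77%.

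**The case against.** The strongest reply is that the comparison is implied. Section 11.1 sizes the trial on two independent proportions, so a between-arm comparison was plainly in mind, and McNemar may be meant only as a supplement. This is fair as to intent, and it makes the repair easy. It does not supply the test: section 11 spells out arm comparisons for transit time and for baseline variables, and none for symptoms.

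Second, the size of the problem is assumed. With no net change the false-positive rate is below 1%, and at 10% one-way improvement with 25 patients it is about 3%, hardly any inflation. If half the arm are stable lactulose users who do not change and 20% or 30% of the rest improve, the figures are 3% or 16%. Entry on three months of symptoms may also limit regression to the mean. All of this stands, so the 38% and 81% figures are unfavourable cases and not expectations.

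Third, the plan cannot strictly be followed as written. McNemar needs a yes/no outcome, no cut-off is defined, and the text does not say whether the test is run per arm or pooled. This also stands. The figures above assume a dichotomy and a test in the probiotic arm.

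A reader might infer that permitting lactulose is itself the error. The documents do not support this. The permission applies to both arms, nothing shows that use will rise or differ, and probiotic versus placebo on top of as-needed lactulose is a sound question. The missing test would be a defect with no lactulose at all. Nor does the trial lack arm comparisons altogether, because transit time has them.

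**Conclusion.** The point holds for constipation symptoms. The first primary objective is a comparison with placebo, the sizing formula is a comparison between groups, and the only named symptom analysis is a change from baseline that cannot answer either. Two within-arm p-values side by side do not repair it.

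The missing test follows from the text alone. The size of the consequence does not: across the assumed rates, a spurious significant improvement in the probiotic arm ranges from 0.4% to 81% with 25 patients, and is well above 2.5% once improvement clearly outweighs worsening. Entry on Rome III makes that direction of change likely but does not fix its size.

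The 80% and 84% power figures depend on the plan's 73.7% versus 36.8%, which section 11.1 words as a fall over 3 weeks. If the placebo arm also improved, to 60% or 50% constipated against 36.8%, a normal approximation gives power of 43% or 17% with 30 per arm. The change makes the symptom question answerable; it does not guarantee that the trial is large enough.

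**What to change.** In section 11:

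1. Make the primary symptom analysis a between-arm comparison of the proportion still constipated at week 8, regardless of laxative use, and state that it addresses probiotic versus placebo on top of as-needed lactulose. Report the difference in proportions with a 95% confidence interval and a chi-squared test.
2. Define constipated, for example as 2 or more of the six Rome III symptoms taken from Garrigues Q9 to Q13 (often or always) and Q15 (under 3 per week), asked with reference to the treatment period.
3. Keep the lactulose permission, and report laxative, suppository and enema use (Q16 to Q18) by arm descriptively.
4. Treat within-arm McNemar results as descriptive.

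The cost is wording and analysis time, with no new visit, instrument or patient. A binary definition must be written, though McNemar needs one too. The Garrigues items as printed have no recall window, so a week-8 answer may describe long-standing habit unless the period is stated when they are asked; stating it is a small change to the questionnaire. The interval will be wide: at the plan's proportions with 25 per arm, 1.96 × √[(0.193831 + 0.232576)/25] = about ±26 points.

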37. Dupont WD, Plummer WD: "Power and Sample Size Calculations: A Review and Computer Program", Controlled Clinical Trials 1990; 11:116-28.

| **[figure not shown]** | **THE EFFECTIVENESS OF PROBIOTICS**  **IN PARKINSON DISEASE WITH CONSTIPATION**  **(SCREENING FORM)** | **[figure not shown]** |
| --- | --- | --- |

(Sticker)

Name :

IC No :

UKM MRN No :

Sex : Male / Female

Age :

Race : Malay / Chinese / Indian / Others

Religion : Islam / Buddhist / Hindu / Christian / Others

Body weight :

Height :

BMI :

Duration of Parkinson Disease:

Disease severity (MDS - UPDRS):

Fulfill Rome III Criteria – Constipation : YES/NO

|  | | | | | | |
| --- | --- | --- | --- | --- | --- | --- |
| Indicated the amount of fibre in your diet: | | | | |  | |
|  | Low (less than 3 servings per day) | | | |  | |
|  | Medium (3-5 servings per day) | | | |  | |
|  | High (more than 5 servings per day) | | | | *1 serving = ½ cup | |
|  |  | | | |  | |
| How often do you perform physical exercise? | | | | |  | |
|  | |  |  |  |  |  |
|  | Sedentary (less than 4 hour per week) | | | |  | |
|  | Non Sedentary (more than 4 hour per week) | | | |  | |
|  | | | | |  | |
| Current medications: | | |  | Previous colonoscopy(within 5 years) | | |
|  | | |  | Year | | Diagnosis |

| Fecal occult blood screening |
| --- |
|  |

| Name:  MRN:  (Sticker) |  | Day 0 |  |  |
| --- | --- | --- | --- | --- |
|  |  | Date | / / 2018 | |

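### Section 10.1, read literally, runs the occult-blood screen before written consent, and sections 5.1 and 9.1 do not settle the order

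*Combined protocol and SAP*

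**What the plan says.** All references are to the combined protocol and SAP.

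- **Consent, section 10.1:** "Written informed consent will be obtained from all subjects after screening inclusion and exclusion criteria".
- **Occult-blood test, section 10.1:** it is item 2 under the screening assessments, after the Rome III module: "Fecal occult blood testing - negative test will be included in the study".
- **Exclusion 4, section 9.2:** "Positive stool occult blood in the last 1 month".
- **Inclusion criteria, section 9.1:** written informed consent is the third criterion.
- **Section 5.1:** patients who meet Rome III are eligible "and will be provided written informed consent". After a passage on lactulose comes the test: "Fecal occult blood testing will be used to screen for colorectal malignancy in all eligible patients prior to intervention". The stated consequence is that "positive test patients will not be included in the study". Only then does 5.1 place something expressly after consent, namely the collection of demographic data.
- **Flow chart, section 12:** the screening box holds Rome III, a negative occult-blood result and the entry criteria. No consent step appears in its readable text.
- **Ethical issues, section 13:** consent is described for patients who agree to be enrolled.
- **Budget, section 15:** 120 occult-blood tests at RM 15 are charged to the study.

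**The concern.** The test is a study procedure: the study pays for it and its result decides entry. Its stated purpose is to look for colorectal malignancy, so a positive result means something to the patient whether or not that patient joins the trial. If the test precedes consent, the people most affected are those who test positive. They have had a research test with a potentially serious implication, they are then excluded, and the consent step in 10.1 never reaches them. The screening form also takes identifying details, current medication and colonoscopy history alongside the test result.

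Separately, the sections describe a positive result in different terms, with a time window in one place and none in the others. A site could be unsure how to treat a patient with an older positive result.

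**Working it through.** No statistical figure is at issue, so the check is a comparison of the sections.

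**Order of consent and test**

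1. Section 10.1 puts consent after the inclusion and exclusion criteria have been screened.
2. Section 10.1 names the occult-blood test as a screening assessment and requires a negative result.
3. Section 9.2 makes a recent positive result an exclusion criterion. A positive result on the trial's own test falls within that window.
4. From 1 to 3, screening is incomplete until the test result is known, so consent under 10.1 follows the test.
5. Section 9.1 lists consent among the inclusion criteria. Consent cannot wait until all inclusion criteria have been screened if it is one of them. The two sections are circular.
6. Section 5.1 can be read either way. Consent is mentioned before the test, in the sentence on Rome III eligibility. But the test is tied only to taking place before the intervention, and the one item expressly placed after consent is demographic data.
7. The flow chart and section 13 do not repair this. The first shows no consent step in its readable text, and the second speaks only of patients who agree to be enrolled.

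**Status of a positive result**

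| Situation | 5.1 | 9.2, exclusion 4 | 10.1 and flow chart |
| --- | --- | --- | --- |
| Positive on the trial's own test | Out | Out | Out |
| Earlier positive within the past month, negative now | Not clear | Out | No bar |
| Positive five weeks ago, negative now | Not clear | No bar | No bar |

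The entries for 5.1 are unclear because it does not say whether it means the trial's own test or any earlier test as well. No section mentions a repeat test or rescreening, in either direction.

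**Budget figure**

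120 × RM 15 = RM 1,800, as stated. 120 / 60 planned patients = 2 tests per patient. This fits 120 people tested once or 60 people tested twice. The carmine line is also 120, which matches two administrations for each of 60 patients. The figure therefore does not show how many people who never enrol would be tested.

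**The case against.** The best defence is that consent may come first in practice. Section 10.1 begins by inviting patients to participate, and its consent sentence stands before the list of screening assessments. Screening the criteria could mean a check of records, followed by consent and then the test. Section 5.1 mentions consent before it mentions the test. The consent pages are not in the text available for this review, so what patients are told about the stool test cannot be seen. This shows that the intended order may be sound. It does not change what 10.1 says, because the test is itself called a screening assessment and no section states that consent precedes it.

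On the positive result, a reader might infer more than the documents support:

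- **That a patient who failed the screen can re-enter after a month.** The entry rules apply together. Sections 5.1 and 10.1 and the flow chart all turn on a negative screening test, and exclusion 4 can be read as an added look-back over earlier results. No section permits rescreening. The documents are silent on it, which is a different matter.
- **That the one-month window is a safety gap.** That would judge a clinical eligibility rule, which is for the investigators. The documents show only that the wording differs.
- **That the colonoscopy entry on the screening form, "Previous colonoscopy(within 5 years", serves no criterion.** No criterion names it, but exclusion 2, on earlier small- or large-bowel disease, can draw on it.
- **That 120 budgeted tests measure the number of unconsented people tested.** The figure has more than one explanation.

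**Conclusion.** The consent point holds. On the wording of 10.1 a study-funded malignancy screen precedes written consent, 9.1 is circular with it, and 5.1 leaves the order open. In scope it applies to everyone who is given the test under 10.1; the number cannot be derived. It rests on two assumptions: that 10.1 is followed as written, and that the consent pages, which were not available, contain no separate consent to screening.

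The point on positive results is smaller. Sections 5.1 and 9.2 use different terms but can be applied together, so this is missing detail on look-back and rescreening, not a flat contradiction.

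Neither point affects the sample size, alpha or power.

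**What to change.** In section 10.1, replace the sentence on consent with one to this effect: *Written informed consent will be obtained before the faecal occult blood test and before any other study-specific screening procedure.* Then align the other places:

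- in 5.1, state that the test follows consent;
- in 9.1, make clear that consent comes first and is not held back until the other criteria have been assessed;
- in the flow chart, add a consent step ahead of the screening box.

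For reconciliation only: the investigators should bring 5.1, 9.2 and 10.1 to one rule of their choosing on what a positive result means for entry, over what period, and whether a repeat test or rescreening is allowed. The clinical content of that rule is theirs to decide.

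The cost is a few sentences and one box in the flow chart. The small downside is that consent is also taken from patients who later fail screening.
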